## Introduction

### Background

Atrial fibrillation (AF) and atrial flutter are prevalent in the USA and are likely to escalate as the population continues to age. These atrial arrhythmias have a substantial impact on quality of life and patient health, increasing the risk for heart failure, thromboembolism, hospitalization, and death. The economic burden on the health care system is considerable [1, 2].

Patients with symptomatic AF and atrial flutter often present to the emergency department (ED) for treatment. There is no definitive evidence supporting optimal ED management of patients with AF and atrial flutter. Treatment strategies vary widely between countries, within countries, and within facilities [3–8]. Not all of this variation is warranted [9]. Implementation of professional society-based guidelines may help standardize care around best practices. But professional society-based guidelines for AF treatment vary in the amount of attention given to emergency medicine-related issues and offer variable recommendations for acute management [10–14].

Using recommendations from various clinical practice guidelines, as well as from primary studies and internal best practices, we created a set of recommendations for emergency medicine physicians in our integrated healthcare delivery system, addressing three leading aspects of ED care: (1) achieving sustained rate reduction for patients with rapid ventricular response; (2) optimizing cardioversion by increasing first-shock success or using suitable pharmacologic agents; (3) increasing implementation of stroke prevention actions in eligible patients being discharged home. By improving rate reduction and cardioversion, we sought to reduce hospitalization in patients with isolated AF or atrial flutter, at least in medical centers with higher hospitalization rates [15]. By promoting stroke prevention actions, we sought to increase the 30-day incidence of anticoagulation initiation for eligible patients.

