#### Analytics and sample size

The aim of the O’CAFÉ trial was to determine whether the intervention reduces hospitalization among eligible ED patients with isolated AF or atrial flutter. We also aimed to determine if the intervention was associated with increased initiation of oral anticoagulants among eligible patients at high stroke risk. To this end, we designed the trial as a superiority trial to determine if intervention sites had better outcomes than control sites.

Analysis of RISTRA-AF effectiveness will be based on comparison of intervention and control groups according to the stepped-wedge cluster randomized pragmatic trial design. All analyses for this stepped-wedge group-randomized trial will be approached using mixed model regression methods. As this is a group-randomized trial and all groups will receive the intervention, all analyses will be done as intent-to-treat. Because the CDSS is available to all ED physicians at each study site and training is given at the site level as part of the intervention initiation, all patients at a given facility will be seen by a physician with access to and knowledge of the CDSS and therefore meet the study definition of “treated.” We will not depend upon CDSS utilization data to identify patients who received CDSS-enhanced care, because as physicians became more familiar with the CDSS content and internalized it, they would be less likely to use the tool during a patient encounter but still deliver care in accordance with the CDSS recommendations. Outcome and predictor measures were derived from the EHR, based on operational processes. We will examine within- and between-cluster correlation over time to elucidate possible correlation structures, including possible time decay in the correlation over time. While intraclass correlation and the number of repeated individuals in our cohort are expected to be low based on pilot study data, we will describe the intraclass correlation and churn rates over time and by cluster. We will use descriptive statistics to examine outcome trends over time overall, by cluster and by intervention status. Following the methods for open cohort stepped-wedge designs with binary outcomes outlined by Li et. al [125], we will use mixed models to allow for clustering with appropriate correlation structures, adjusting for time effects, RISTRA-AF status, and possibly hospital-level fixed effects.

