We estimate that our stepped-wedge design (with nine clusters and 10 steps) will include approximately 3420 adult ED encounters with primary and 972 (30%) with isolated AF or atrial flutter during the 10-month roll-out period. Based on pilot data, we expect at least 567 patients in the usual care condition and 460 patients in the intervention condition with isolated AF or atrial flutter during the 10-month roll-out period. Using preliminary data at the pilot sites and the trial sites, baseline initial hospitalization rate was 26.6%. We estimate a minimally detectable 8% absolute difference in initial hospitalization rate (Aim 1) at a level of 90% power and a 2-sided test at the 2.5% significance level.

We estimated the minimum number of clusters needed to achieve 90% power based on pilot data using the National Institute of Health Stepped-wedge Group Randomized Trial Calculator [126]. We present our most conservative estimates here. For the hospitalization outcome, we assume an average of 11 eligible encounters per cluster, intraclass correlation of 0.01, the cluster autocorrelation of 0.47, and the individual autocorrelation of 0.9 with a discrete-time decay, a churn rate of 0.942 and adjustment for one cluster-level variable (annual ED census) with R [2] of 0.07. We would need only three clusters to see a decrease of 8% in hospitalization rates at 90% power, so we believe that we have adequate power in this analysis, given data from nine clusters over the course of the trial.

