Given that only 18% of ED encounters are eligible for stroke prevention action (discharged to home, current KP member, not currently or recently taking oral anticoagulants, and at high risk for stroke), the overall numbers of eligible encounters for the stroke prevention-related outcomes are much smaller. For the primary Aim 2 outcome (any prescription ordered for oral anticoagulation medications within 30 days of the index visit), power is still adequate in this study design to identify changes in rates of prescriptions ordered as small as 5% in the eligible subgroup. Based on pilot data and assuming an average of seven eligible encounters per cluster, intraclass correlation of 0.006, the cluster autocorrelation of 0.356, and the individual autocorrelation coefficient of zero with a discrete-time decay, and a churn rate of 0.984 with no adjustments for cluster-level variables, our nine-cluster design will allow us to identify a 4.9% change in rates of anticoagulant prescription with 80% power.

We anticipate wide variation in practice patterns across our EDs, as we have seen in the management of other conditions [54, 127, 128]. Some EDs might start the trial further from their optimal performance level than others. These EDs may have more potential for practice improvement than others and more to gain from the intervention. To account for this, we will also report facility-specific changes from pre- to post-intervention, anticipating a larger impact at facilities whose pre-intervention practices were in the lower tertile.

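### If EDs are ranked on the same control months that supply their pre value, regression to the mean alone gives the anticipated larger gain in the worst tertile, about 3 to 8 points for hospitalization

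*Protocol article*

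**What the plan says.** The last paragraph of Analytics and sample size starts from the premise "We anticipate wide variation in practice patterns across our EDs" and reasons that EDs further from their best performance have more to gain. It then commits to the report: "we will also report facility-specific changes from pre- to post-intervention, anticipating a larger impact at facilities whose pre-intervention practices were in the lower tertile". The measure of practice and the months that define the tertile are not given.

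The same section sets the general method: "All analyses for this stepped-wedge group-randomized trial will be approached using mixed model regression methods", with models "adjusting for time effects, RISTRA-AF status, and possibly hospital-level fixed effects". The Background already points towards low-performing sites, since the hoped-for reduction in hospitalization is expected "at least in medical centers with higher hospitalization rates".

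**The concern.** An ED's baseline rate appears twice. It decides whether the ED falls in the worst tertile, and it is subtracted to form the change. An ED whose control months were bad by chance is more likely to be placed in the worst tertile, and it is then credited with an improvement when its rate returns to its usual level. The pattern the article says it expects is the pattern this selection produces when the tool does nothing.

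What is at stake is the reading of the facility report. A larger gain at low-performing EDs could be taken as evidence that the tool works there and should be targeted there. The temptation would be greatest if the overall result were null.

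**Working it through.** The article gives no figure for the facility report, so there is none to reproduce. The Aim 1 planning statement, "a minimally detectable 8% absolute difference in initial hospitalization rate (Aim 1) at a level of 90% power", serves only as a yardstick, and nothing below depends on that power figure.

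**Inputs from the article**
- Baseline hospitalization 26.6%; ICC 0.01; cluster autocorrelation 0.47.
- 11 encounters per cluster, read as per month because 11 × 9 clusters × 10 months = 990, close to the stated 972. Per ED: 11 × 9 / 13 = 7.6 per month.
- 13 EDs in nine clusters. Control months run from 3 (first sequence) to 11 (last). Two transition months are dropped from 22, so post months = 20 − control months.

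**Assumptions**
- Encounters split equally over EDs, and the ICC applied at ED level.
- Tertile taken as 4 of 13 EDs, ranked on their own control months.
- No intervention effect and no time trend.

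**Step 1: noise in one ED's baseline.** Binomial variance per encounter = 0.266 × 0.734 = 0.1952.
- 3 control months: √(0.1952 / 22.8) = 9.2 points.
- 11 control months: √(0.1952 / 83.8) = 4.8 points.
- True between-ED SD at ICC 0.01: √(0.01 × 0.1952) = 4.4 points.
- Share of baseline variance that is noise: 0.00855 / (0.00855 + 0.00195) = 81% at 3 months; 0.00233 / (0.00233 + 0.00195) = 54% at 11 months.

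**Step 2: approximate size.** Expected spurious change ≈ noise share × 1.07 × SD of observed baselines. Here 1.07 is the expected mean of the top 4 of 13 standard normal values. Sampling variance averaged over 3 to 11 control months is 0.1952 / 7.615 × 0.1689 = 0.00433, where 0.1689 is the mean of 1/m for m = 3 to 11.

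| Between-ED SD | Noise share | SD of baselines | Spurious change |
|---|---|---|---|
| 4.4 points (ICC 0.01) | 69% | 7.9 points | 5.8 points |
| 10 points (assumed) | 30% | 12.0 points | 3.9 points |
| 15 points (assumed) | 16% | 16.4 points | 2.8 points |

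**Step 3: simulation with stable ED rates.** This used 8,000 null trials with binomial outcomes and randomised sequences. At ICC 0.01 the worst four EDs change by −5.9 points and the other nine by +2.6. Weighted over facilities, (4 × −5.9 + 9 × 2.6) / 13 = −0.02, which is about zero. The worst tertile appears to improve in 94% of null trials. At SD 10 and 15 points the change is −4.1 and −3.1.

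**Step 4: simulation adding the cluster autocorrelation of 0.47.** Part of each ED's deviation now fades with time, so more of the baseline extreme is lost by the post period.

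| Persistent between-ED SD added | All control months | Common first 3 months only |
|---|---|---|
| 0 | −7.8 | −10.9 |
| 5 points | −6.3 | −9.8 |
| 10 points | −4.5 | −7.8 |
| 15 points | −3.5 | −6.4 |

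In the first row the worst tertile goes from 34.4% to about 26.6%, and its change passes −8 points in 46% of null trials. At SD 15 with all control months it does so in 16%.

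**Step 5: Aim 2.** Inputs are 7 encounters per cluster, ICC 0.006 and cluster autocorrelation 0.356. The base rate is not given, so 20% to 60% was assumed. The lowest-prescribing tertile appears to gain about 8 to 10 points with the article's ICC alone, and about 3 to 7 points with a between-ED SD of 10 to 15 points, using all control months.

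**Step 6: does the stated model remove it?** Calendar-time terms remove a trend common to all EDs, but the excess in the selected EDs is particular to them. Hospital fixed effects take each ED's own baseline at face value, without shrinkage. As described, the model has a single RISTRA-AF term, with no facility-specific effect and no interaction with baseline.

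**The case against.** Four arguments on the other side carry weight.

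- **Not stated to be raw.** A reader might infer unadjusted pre-to-post differences with no allowance for calendar time. The article does not say so, and its statement that all analyses use mixed models with time effects points the other way. This stands, and no criticism of time adjustment is made here. Selection on baseline survives the adjustment (Step 6).
- **Ranking source not stated.** Tertiles might come from earlier facility data or from a process measure, either of which would weaken or remove the artefact. The article does mention preliminary data from the trial sites. This stands as a condition on the point. How tertiles are set could be left to an analysis plan. The point is that the quantity and its expected direction are already fixed, and the natural reading of them is the vulnerable one.
- **Size depends on the spread between EDs.** The statement that most of the baseline spread is noise holds at ICC 0.01 but not under the wide variation the article expects. The artefact then roughly halves, without disappearing.
- **Supplementary status.** The report is an addition, with no test or decision rule attached. This stands and limits the importance of the point.

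A reader might also set the 8.5-point gap between tertiles (5.9 + 2.6) against the 8-point target. That compares a contrast between subgroups with a main effect. The like-for-like figure is 5.9, or 7.8 with the cluster autocorrelation.

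**Conclusion.** The point holds on condition that the tertile is set from the same control months that form the pre value. With no true effect, the worst tertile would then appear to improve in hospitalization by about 6 points under the article's ICC, about 8 with its cluster autocorrelation added, and about 3 to 4.5 if the between-ED SD is 10 to 15 points. The last range rests on an assumed SD, because the article gives no figure for the wide variation. All figures assume equal encounters per ED and a monthly reading of the 11 encounters.

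Two stronger conclusions are not supported. It cannot be said that the report will show a large effect, since that depends on the ranking source and the true spread. Nor does the trial's main result suffer: the artefact averages to about zero over facilities and does not enter the primary stepped-wedge estimate. The risk is confined to a misleading claim about which EDs benefit.

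**What to change.** - Set tertiles from facility data that precede the trial's control months. The preliminary trial-site data behind the 26.6% would serve if they exist by facility for all 13 EDs; the article neither dates them nor says so. Otherwise use an EHR extract from before July 2021. State the measure and the window.
- Assess the expectation of a larger impact as a RISTRA-AF by tertile interaction in the time-adjusted mixed model.
- Report facility effects as shrunken estimates (random intervention effect by facility) with intervals.
- Label any unadjusted facility changes as descriptive, and note that regression to the mean is expected in the extreme tertiles.

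The cost is a wording change, slightly more analysis and possibly one further data extract. The interaction will be imprecise with 13 EDs in nine clusters, and the report should say so.

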#### Dissemination policy

We will use authorship eligibility criteria from the International Committee of Medical Journal Editors. We intend to disseminate our results within the medical group and health system. We also will submit abstracts for presentation at professional society meetings and submit manuscripts to clinical journals for peer review.

## Discussion

We are implementing a stepped-wedge cluster randomized pragmatic trial, O’CAFÉ, to evaluate the effect of RISTRA-AF, an electronic CDSS integrated into the EHR, to improve care of ED patients with AF or atrial flutter. The tool addresses comprehensive ED management, which includes administration of long-acting rate-reducing medications, best practices for more effective, time-efficient cardioversion, and identification of and recommended actions for AF and atrial flutter patients at increased predicted risk for ischemic stroke (Table 1). We hypothesize that the intervention will be associated with reduced initial hospitalization (Aim 1) and increased 30-day anticoagulation initiation (Aim 2).

There have been few randomized trials in the ED implementing best practices to improve the care of patients with AF or atrial flutter. RAFF-3 was such a trial, a stepped-wedged cluster randomized trial conducted across 11 EDs in Canada [98]. Investigators implemented the 2021 Acute AF/Flutter Best Practices checklist from the Canadian Association of Emergency Physicians [12]. The trial’s primary aim was to reduce ED length of stay by promoting ED cardioversion over a rate-reduction strategy. They also sought to increase anticoagulation initiation at the time of discharge in eligible patients. The study population included only hemodynamically stable patients presenting with an episode of “acute” AF or atrial flutter of at least 3 h duration, where symptoms required ED management by rhythm or rate control. Patients with permanent AF or atrial flutter were excluded. Over 90% of enrolled patients had presumed recent-onset AF or atrial flutter < 48 h in duration. The intervention increased the proportion of patients undergoing attempted cardioversion (from 67 to 85%), reduced the use of rate control measures (from 54 to 38%), increased the proportion of patients with sinus restoration (from 76 to 86%), and reduced ED length of stay by 21% [98]. There was no improvement in new anticoagulation prescriptions at the time of ED discharge.

The O’CAFÉ trial differs in several ways. We included a broader population of patients with AF and atrial flutter; we did not limit eligibility by hemodynamic stability or arrhythmia duration, for we sought to address care for a wide spectrum of patients with primary AF and atrial flutter. Our strategy of recommendations was also different. Unlike the RAFF-3 trial, we did not seek to increase cardioversion and decrease rate control strategies, even for patients with presumed recent-onset AF or atrial flutter. We let the treating physician decide whether rhythm or rate control was indicated, only reminding them of when different strategies might be appropriate. Our rate and rhythm recommendations focused on ways of optimizing the chosen intervention. For the physician pursuing cardioversion, for example, we recommend methods to increase first-shock success. For the physician pursuing rate reduction, we recommend long-acting medications that facilitate sustained rate reduction and have been associated with reduced hospitalization.

Other ED-based trials have addressed more specific questions of AF management among subpopulations of ED AF patients, e.g., rapidity of rate reduction (intravenous diltiazem vs intravenous metoprolol) [72, 73], method of cardioversion (pharmacologic vs electrical) [129, 130], medication of cardioversion (e.g., intravenous vernakalant vs intravenous ibutilide) [131], timing of cardioversion (early vs delayed) [82, 83], and location of acute management (observation unit vs inpatient ward) [132].

Our decision support application did not have only treating physicians in view. We were equally mindful of our patients. Reducing hospitalization, one of our study aims, is an outcome valued by patients [133, 134]. Symptom reduction is also highly prized by patients. We pursued this patient-centered outcome by seeking to improve sustained rate reduction and increase the success of cardioversion, both of which reduce symptoms caused by the rapid ventricular response common in patients with AF and atrial flutter.

In sum, we describe the design of a CDSS to aid in the comprehensive management of ED patients with AF or atrial flutter, its pilot in three EDs, and its implementation using a stepped-wedge cluster randomized trial across 13 EDs of an integrated care system in northern California. This trial sought to improve uptake of best practices, improving measures of rate reduction, cardioversion, and stroke prevention. In particular, the study aimed to reduce hospitalization and increase anticoagulation prescribing for eligible patients. We will publish our results upon study completion.

## Trial status

Protocol version 10 (13 February 2023); enrollment (recruitment) start date: 1 October 2022; projected enrollment (recruitment) completion date: 30 April 2023.

## Data Availability

Not applicable.

## Abbreviations

AF: Atrial fibrillation
CDSS: Clinical decision support system
ED: Emergency department
EHR: Electronic health record
O’CAFÉ trial: Clinical decision support to *O*ptimize *C*are of patients with *A*trial *F*ibrillation or flutter in the *E*mergency department trial
RISTRA: Risk stratification application
